### Intervention Group

The day before their surgery, patients will receive an email or SMS notification encouraging them to access the LeoMed platform. The platform prompts patients to click on links that direct them to the digital portal of the CHUM website, where all health sheets describing the perioperative pathway are published and grouped together, and preoperative psychological empowerment video resources are available that have been specifically created with the help of the CHUM communications service.

Postoperatively, notifications will be sent to the participants every day during the first 4 days. These notifications will direct patients to online forms assessing their medical condition. The questionnaires used are derived from the Brief Pain Inventory [18] and the Institut national de santé publique du Québec (INSPQ; Quebec Public Health Expertise and Reference Center in English) [19], which suggests using a simple questionnaire with 4 items for identification of surgical site infections. The items include redness at the surgical site, presence of pus at the surgical site, fever, and wound pain.

The LeoMed platform will automatically classify patients’ responses using an artificial intelligence algorithm and generate alerts on the home page. The home page is displayed on a giant screen on CHUM’s telehealth service, which will offer tailored support according to patients’ clinical need.

Health support will be provided by CHUM’s telehealth service, which comprises a team of 50 nurses. This department is a 24/7 call center that manages many telecare platforms dedicated to remote patient support for various medical specialties. All the staff of this service are trained in new technologies. Their mission is to provide health care remotely and to coordinate the interventions of different medical and paramedical personnel within the hospital. Specifically for this project, patient responses appear on a giant screen in the main open space where the CHUM telehealth service nurses work. In the event of an alert, a nurse will contact the patient within a maximum of 8 hours and provide appropriate care.

On postoperative day (POD) 15 and 30, the LeoMed platform will send a follow-up form that aims to evaluate all indicators considered in the medicoeconomic analysis. All the indicators are detailed in Table 1.

**Table 1 table1:** Schedule of enrollment, interventions, and assessments.

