**Assessments on** **the LeoMed platform**															
	Quality of life (EQ-5D-5L visual analogue scale)	✓												✓	
	Unplanned readmissions													✓	
	Unplanned visits (eg, family doctor, walk-in clinic)													✓	
	Emergency department visits													✓	
	Calls to CHUM^b^ online support													✓	
	Calls to the Quebec health information line													✓	

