### Control Group

Participants assigned to the control group will be followed up according to usual care, which consists of a telephone call the day before the procedure as a reminder of safety instructions. Postoperative follow-up is not standardized and remains specific to each surgical specialty. Access to a limited version of the LeoMed platform will also be given to these participants during the preoperative clinic visit. This version includes a preoperative questionnaire and follow-up forms at POD 15 and POD 30 that are identical to those received by the intervention group and collect the indicators considered in the primary analysis (Table 1). Like the patients in the intervention group, the control patients will have 24/7 access to the provincial or CHUM health information lines, if needed.

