### Primary Outcome

The primary outcome will be the cost-effectiveness of the LeoMed telecare platform deployment assessed by its direct costs, including unanticipated cancellations on the day of surgery due to preoperative instructions not being followed, calls to the local CHUM health information line, calls to the Quebec health information line (ie, 811), visits to the emergency department, and unplanned readmissions or medical visits (to family doctors or outpatient clinics) for problems related to the procedure within the first 30 days after the procedure.

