### Data Analysis

Data analysis will be performed by a team of researchers at the École des Hautes Études Commerciales in Montreal, Quebec, using SPSS (version 28; IBM Corp). All data will be analyzed according to the intention-to-treat principle. Descriptive statistics will be reported as frequencies and proportions for categorical data and means and standard deviations for continuous variables. Demographic data for the 2 groups of patients will be compared using the Mann-Whitney *U* test (for ordinal data), the chi-square test (for nominal data), and a 2-tailed *t* test (for continuous data).

Considering the Canadian guidelines for the economic evaluation of health technologies [22], the perspective of the health care system will be privileged in this study. Specifically, 2 main types of analyses will be carried out. First, all interventions in both groups related to surgery (calls to the provincial or CHUM information lines, visits to the ambulatory unit, hospital readmissions, and visits to the emergency department) will be recorded during the study to perform the cost-effectiveness analysis. Second, a cost-utility analysis will be conducted to quality-weight each effectiveness outcome measured in QALYs. QALYs will be calculated as life with the health state under study multiplied by the utility associated with that health state. CHUM’s internal data will be used to determine the cost of health care staff and the average cost of an emergency room visit for the clientele concerned in fiscal year 2019-2020. For hospitalizations, we will use the average costs calculated according to the American diagnosis-related groups method, which was applied at CHUM in 2019-2020. Technology costs will be estimated based on license prices in effect at the time of the study and amortized on a straight-line basis over a 5-year period. All calculations will be in Canadian dollars. Last, patient satisfaction with care services will be measured in both groups at the end of the trial using Likert scales adapted from Sicotte et al [23]. This protocol follows the SPIRIT (Standard Protocol Items: Recommendation for Interventional Trials) 2013 Statement for trial protocols [24].

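### The primary outcome and Table 1 count only 'unplanned' visits and readmissions, while Data Analysis records all surgery-related care; the narrower rule may count less in the platform arm

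*Protocol article*

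**What the plan says.** **Primary Outcome.** Among the cost components within 30 days are "unplanned readmissions or medical visits (to family doctors or outpatient clinics) for problems related to the procedure". Emergency department visits and calls to the two information lines are listed there without the word 'unplanned'.

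**Table 1.** The restriction is repeated in the items assessed on the LeoMed platform: readmissions are labelled unplanned, and the visit item reads "Unplanned visits (eg, family doctor, walk-in clinic"). The items assigned to the electronic record are same-day cancellations and calls to the hospital's own line.

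**Data Analysis.** For the cost-effectiveness analysis the plan will record "all interventions in both groups related to surgery". Besides calls, the list contains "visits to the ambulatory unit, hospital readmissions, and visits to the emergency department". The word 'unplanned' does not appear, and neither do family-doctor visits.

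**Intervention Group.** Postoperative questionnaires generate alerts. "In the event of an alert, a nurse will contact the patient within a maximum of 8 hours and provide appropriate care". The mission of the telehealth department includes to "coordinate the interventions of different medical and paramedical personnel within the hospital".

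**Control Group.** "Postoperative follow-up is not standardized and remains specific to each surgical specialty". Also, "the control patients will have 24/7 access to the provincial or CHUM health information lines, if needed". The day 15 and day 30 forms are the same in both arms.

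**The concern.** Whether a visit enters the endpoint depends on a label, and the randomised intervention can influence that label. Take two patients with the same wound problem. One answers a symptom form, triggers an alert, speaks to a nurse and is seen at the hospital. The other goes to a walk-in clinic, which is Table 1's own example of an unplanned visit. Asked on day 30 about unplanned visits, the first may reasonably answer no and the second yes. Both visits cost the health care system money, and that is the perspective the analysis adopts.

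The Introduction expects the platform to reduce unplanned visits and readmissions. Real prevention and a shift from self-initiated to arranged care would both appear as success under the narrower rule, and the endpoint could not separate them. Patients fill in the forms knowing their allocation, so blinding the statisticians does not protect this step.

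**Working it through.** The article gives no figure on this point to reproduce, so the check compares the counting rules and then illustrates what the difference could do.

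**Step 1: the rules side by side.**

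| Contact | Primary Outcome and Table 1 | Data Analysis |
|---|---|---|
| Hospital readmission | only if unplanned | listed, no restriction |
| Outpatient or ambulatory visit at the hospital | only if unplanned | listed, no restriction |
| Family-doctor visit | only if unplanned | not listed |
| Emergency department visit | counted | listed |
| Calls to either line | counted | listed |

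The rules agree on the last two rows and differ on the first three. Under the narrower rule, an arranged hospital visit may be left out. Under the wider rule it is counted, but if the list is exhaustive a component named in the primary outcome disappears. That second omission need not favour the platform, since controls may rely more on community care.

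**Step 2: would existing data capture settle it?** Data Collection provides calls for missing or incomplete day 30 forms, personal contact when an event is reported, and cross-referencing with the hospital record. A form that is complete but omits an arranged visit triggers neither kind of call. The hospital record can show a visit at the hospital, but it does not decide whether that visit was unplanned, and the article does not say that it captures care given elsewhere.

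**Step 3: size, by assumption.** Let true use be equal in both arms. Let qI and qC be the shares of procedure-related visits or readmissions left uncounted as planned in the intervention and control arms. Then

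observed ratio = (1 − qI)/(1 − qC).

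- qI = 0.25, qC = 0.25: 0.75/0.75 = 1.00, no distortion.
- qI = 0.25, qC = 0.10: 0.75/0.90 = 0.83, a spurious reduction of 17%.
- qI = 0.50, qC = 0.10: 0.50/0.90 = 0.56, a spurious reduction of 44%.
- qC = 0: the spurious reduction equals qI.

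The same ratio applies to the cost of that component if uncounted contacts cost as much on average as counted ones. The documents give no value for qI or qC.

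**Step 4: an upper illustration in event counts.** The Introduction cites a 30-day readmission rate of 7.3%. No rate is given for medical visits, so readmissions stand in, although they are less likely to be relabelled. With the planned 500 per arm, 0.073 × 500 = 36.5 readmissions; qI = 0.25 would remove 0.25 × 36.5 = 9.1. Set qC = 0, p1 = 0.073, p2 = 0.073(1 − qI), and let p̄ be their mean. The chance of a significant result in the platform's favour (two-sided 5% test of two proportions) is

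Φ{[p1 − p2 − 1.96√(2p̄(1 − p̄)/500)] / √([p1(1 − p1) + p2(1 − p2)]/500)}.

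| qI | observed p2 | chance |
|---|---|---|
| 0.10 | 6.6% | 7% |
| 0.20 | 5.8% | 15% |
| 0.30 | 5.1% | 30% |
| 0.50 | 3.7% | 72% |

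Without relabelling the chance in that direction is 2.5%. These figures bound an extreme case and do not forecast what will happen. The declared primary outcome is cost-effectiveness, not this test.

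**The case against.** The strongest reply is that Data Analysis already counts everything related to surgery in both groups, so a nurse-arranged hospital visit or readmission is recorded. That is right for that section. It leaves the Primary Outcome section and Table 1 saying something narrower, and the form items follow the narrower wording.

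Second, a return for a wound problem is unplanned in ordinary language, whoever referred the patient, and the full protocol or case report form may define the term. This is a fair reading, especially for readmissions, and it is why medical visits are the main exposure. Even so, the published sections conflict.

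Third, a reader might infer that nurses book visits and that events therefore vanish from one arm only. The article does not support this. Booking is an inference from the duty to provide care and from a mission statement covering the whole department. Controls have specialty follow-up and the same information lines, through which care can also be arranged. This part of the objection stands: the asymmetry is one of degree.

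Fourth, identical forms, telephone contacts and the record cross-check reduce the problem. They do so most for care inside the hospital, which is where coordinated care would take place. The remaining gap is a matter of classification, and of visits that a completed form omits.

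**Conclusion.** The article holds two unreconciled counting rules for readmissions and medical visits. The narrower one can respond to the randomised care pathway, and the likelier direction is understated use and cost in the platform arm. This rests on two assumptions: that some care after alerts is arranged through the telehealth service, and that patients or data collectors treat some of it as planned. Neither is stated in the article. Emergency visits and calls are unaffected, and they dilute any effect on total cost. The size cannot be derived, because the article gives neither the shares nor unit costs.

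A reader might also set a relabelled share of one quarter against the 21% reduction in the Abstract and conclude that relabelling alone could reach the trial's target. That comparison is unsound: the Sample Size section shows that 0.21 is an effect size on a recovery score at day 7, not a reduction in visits or readmissions.

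The point is worth correcting because the correction is cheap and analysts could not fully repair the counts afterwards.

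**What to change.** Use one definition in the Primary Outcome section, Table 1, Data Analysis and the day 15 and day 30 forms, for both arms: any procedure-related medical visit or readmission within 30 days that was not already scheduled at discharge from the day surgery, whoever initiated it, including those arranged or advised by the telehealth service. Name family-doctor visits in the Data Analysis list. Cost all such contacts identically in both arms.

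If feasible, add one form item on who initiated the contact, so that arranged and self-initiated care can be shown separately. For patients already followed up, reclassify from the hospital record and the existing telephone contacts where possible, and report how many could not be reclassified.

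The change costs one definition, perhaps one form item, and an amendment requiring ethics approval. Recruitment began in August 2022 and 142 patients were enrolled by 31 October 2022, so some patients may have answered the existing form. The intervention arm's count may rise and make the result less favourable to the platform.

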### Secondary Outcome

The secondary outcome considered for the cost-utility analysis will be quality-adjusted life years (QALYs). According to a recent update of the guide for economic evaluation published by the French National Authority for Health [20], the EQ-5D-5L visual analog scale (VAS) is the preferred measure used to assess quality of life and to derive utility values for use in health technology appraisals. It will be assessed at POD 30 and compared with the preoperative baseline [21]. The EQ-5D-5L VAS is a questionnaire that is well validated. It includes 5 dimensions, each describing a different aspect of health: mobility, self-care, usual activities, pain/discomfort, and anxiety/depression. Patient satisfaction with care services will also be assessed.

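### The protocol names the EQ-5D-5L VAS as the source of utilities but describes the five-dimension questionnaire, so the basis of the QALYs is contradictory

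*Protocol article*

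**What the plan says.** Under Secondary Outcome, the protocol article makes QALYs the outcome for the cost-utility analysis and states that "the EQ-5D-5L visual analog scale (VAS) is the preferred measure used to assess quality of life and to derive utility values". It continues: "The EQ-5D-5L VAS is a questionnaire that is well validated". The next sentence says what this instrument contains: "It includes 5 dimensions, each describing a different aspect of health: mobility, self-care, usual activities, pain/discomfort, and anxiety/depression". On timing: "It will be assessed at POD 30 and compared with the preoperative baseline".

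Table 1, in the block of assessments made on the LeoMed platform, has one quality-of-life row: "Quality of life (EQ-5D-5L visual analogue scale". No descriptive system, profile or index is listed beside it.

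Under Data Analysis, QALYs are computed as time lived in a health state times the utility of that state. The section does not say which EQ-5D-5L component supplies the utility. The Introduction makes cost-utility the secondary objective, and Data Analysis counts it as one of the two main types of analysis.

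**The concern.** The EQ-5D-5L yields two different scores. The five items place the patient in a health state, and a value set then assigns a utility to that state. The VAS is a single rating by the patient of his or her own overall health. It is not a preference weight anchored at death = 0, so multiplying it by time does not give a QALY.

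The protocol gives the VAS the role of the first score and describes it as if it were that score. If the forms and the analysis follow the name, the incremental cost per QALY has the wrong kind of quantity in its denominator. It could not then be compared with other costs per QALY. If they follow the description, the analysis can be sound, but the assessment schedule lists the wrong measure. An analyst working from the text cannot tell which is meant. An analysis plan cannot recover five items that were never asked.

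**Working it through.** There is no stated figure to reproduce on this point. The check is a comparison of the places that name, describe or use the instrument.

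1. **Name.** Secondary Outcome calls it the EQ-5D-5L VAS twice, and Table 1 does so once. All three agree on the VAS.
2. **Role.** Secondary Outcome makes that VAS the measure from which utilities are derived.
3. **Content.** Secondary Outcome then says: "It includes 5 dimensions, each describing a different aspect of health". The five domains listed are those of the descriptive system. A single rating on a line cannot have five dimensions, so steps 1 and 3 cannot describe the same score.
4. **Use.** The formula under Data Analysis needs a utility attached to a health state. The five items define such a state; a single self-rating does not. Step 4 therefore fits step 3 and not step 1.
5. **Collection.** The schedule follows step 1: the VAS is the only quality-of-life measure listed.

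So the name and the schedule point to the VAS, while the description and the formula point to the five-item system. No other section settles it. The Abstract speaks only of a questionnaire for assessing QALYs.

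**What can be said about size.** The most that a patient can accrue over the 30 days is 30/365.25 = 0.082 QALY. Suppose a between-arm score difference D holds over the whole period. Then

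- incremental QALY = D × 30/365.25
- cost per QALY = incremental cost / (D × 30/365.25)

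Replacing the index difference by the VAS difference changes this ratio by the factor D_index / D_VAS. The 30/365.25 term cancels. The relative error therefore depends only on how the two scores differ between arms, and the documents give no values for either. Neither its direction nor its size can be derived.

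**Patients already affected if only the VAS was loaded.** The Results section reports 142 enrolled by October 31, 2022. Against the planned 1000, that is 142/1000 = 14.2%, and the share grows with further enrolment.

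**The case against.** The strongest reply is that VAS is simply a misnomer. The text calls the instrument a questionnaire, lists all five domains, and defines QALYs in terms of health states. A mislabelled full EQ-5D-5L is at least as plausible as a VAS-only plan. This stands, and it rules out saying that the trial has chosen an invalid analysis. It does not remove the contradiction, because the assessment schedule lists only the VAS.

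It is also fair that the choice of value set is commonly left to the analysis plan. Its absence here is no fault, and no particular national set can be required on the strength of this document.

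A reader might go further in two ways that the documents do not support:

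- **French against Canadian guidance.** The instrument is justified by a French guide, while Data Analysis opens with "Considering the Canadian guidelines for the economic evaluation of health technologies". That clause introduces the choice of the health care system perspective. Citing one source for the instrument and another for the perspective is not a contradiction, and no French value set is proposed anywhere.
- **A stated percentage error, or special sensitivity because of the short horizon.** Any percentage would only restate assumed VAS and index differences. The small 30-day ceiling does not enlarge the relative error from using the wrong score, since the time factor cancels.

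**Conclusion.** The inconsistency is certain; its consequence is conditional. If the plan is followed as named and scheduled, the secondary cost-utility result is not a valid cost per QALY. If the full EQ-5D-5L is in fact collected and scored, the result can be sound, and the fault lies in the wording of Secondary Outcome and Table 1. The documents do not show which case applies.

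The point reaches the whole cost-utility analysis and nothing beyond it. The primary outcome is built on direct costs and does not use the EQ-5D-5L. The conclusion rests on one methodological premise, that a self-rated VAS is not a utility for a health state, and on no assumed effect sizes. It goes beyond a clerical slip because the named instrument feeds the stated secondary outcome.

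**What to change.** - **Check the forms first.** Confirm that the five EQ-5D-5L items, and not only the VAS, are on the preoperative and POD 30 forms. Add them if they are not.
- **Correct the text.** In Secondary Outcome, Table 1 and Data Analysis, state that utilities for QALYs come from the five-item descriptive system scored with a value set, which the analysis plan will name. List the descriptive system and the VAS as separate entries in Table 1.
- **Report the VAS separately**, as a descriptive quality-of-life score that does not enter the QALY calculation.

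**Cost.** If the items are already collected, this is a wording change only. If they are not, it means at most five short items added to existing electronic forms. In that case the preoperative utilities of patients already enrolled cannot be recovered, and the cost-utility analysis would have to treat those baselines as missing. That loss grows with each enrolment, so the form check should not wait for the analysis plan.
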